### Objectives and aims

This project will conduct a hybrid type 3 effectiveness-implementation randomized trial to evaluate the effects of BASIS-T on implementation mechanisms and outcomes when applied to positive greetings at the door (PGD), a low-burden, universal EBPP that has been found to reduce disruptive behavior and increase academic engagement [51–53], both important indicators of positive SEB functioning [54–57]. We will also examine for whom, under what conditions, and how efficiently BASIS-T works to improve outcomes.

PGD is a preventive classroom management strategy based on three major themes: (a) classroom climate, (b) pre-correction, and (c) positive reinforcement [53]. PGD has been found to be well aligned with school settings and effective at addressing SEB needs. Multiple studies have found increases in on-task behavior in middle school students, and reductions in latency-to-task engagement in high school students [51, 52]. These findings were replicated in a longitudinal randomized controlled efficacy trial conducted with 203 students across 10 classrooms, finding improvements in academic engagement and decreases in disruptive behavior [53]. However, consistent with more general research on universal EBPPs, results also suggested that some of the teachers delivering PGD struggled with initial adoption, with two of the five teachers in the PGD condition (40%) requiring extra consultative support due to initial low levels of implementation.Aim 1: Experimentally evaluate the effects of BASIS-T versus active comparison control (ACC)

Aim 1 will evaluate the main effects of BASIS-T on proximal mechanisms (attitudes, subjective norms, self-efficacy, intentions to implement, and maintenance self-efficacy), implementation outcomes (adoption, reach, fidelity, and sustainment), and student outcomes (classroom aggregated grades, test scores, attendance, and teacher ratings of classroom on-task behavior, disruptive behavior, and prosocial behavior).*Research question (RQ) 1a.* Is BASIS-T more effective than the ACC condition at producing changes in proximal mechanisms of behavior change?*RQ 1b.* Is BASIS-T more effective than the ACC condition in promoting implementation outcomes?*RQ 1c.* Is BASIS-T more effective than the ACC condition in promoting meaningful changes in student SEB and academic outcomes?Aim 2: Evaluate how, for whom, under what conditions, and how efficiently BASIS-T works to improve outcomes

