#### Teacher and school data collection

Teacher data collection will span both active implementation and sustainment phases (18 months per cohort). Data will include teacher quantitative web-based surveys and qualitative interviews, each of which will be incentivized. To promote data integrity, key items will be forced to choose to prevent unplanned missingness and out-of-range responses. All data will be de-identified and stored securely. Detailed information about all study measures (including citations) can be found in Additional file 4.

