#### Quantitative surveys

Participants will complete secure web-based surveys at 13 timepoints spanning three phases: preparation (times 1–4), active implementation (times 5–11), and sustainment (times 12–13 follow-up during the next academic year) [45]. Time 1 will occur during informed consent, time 2 in the days immediately before BASIS-T/ACC pre-training, time 3 immediately after pre-training, time 4 immediately after post-training, time 5 two weeks after training, time 6 four weeks after training, times 7–11 monthly until the end of the academic year, time 12 at the beginning of the subsequent academic year, and time 13 during the spring of that academic year. Teachers will self-report demographics, perceptions about BASIS-T (when relevant) and PGD training, BASIS-T mechanisms, implementation outcomes, organizational moderators (implementation climate, leadership), and time and resources used for PGD implementation. From times 7–11, to reduce the respondent burden we will use a random item planned missingness design for measures of attitudes (1 item selected per subscale), action self-efficacy (2 items selected), and subjective norms (1 item selected per each scale).

Data collection regarding students will focus on classroom behavior, behavioral discipline, attendance, and academic performance and will be collected in aggregate at the classroom level, without individual identifiers. Teachers will complete the first secure online survey on student classroom behavior at time 4, as earlier data collection would prohibit teachers from having an adequate sample of student behavior. At the end of each school year, academic and behavioral data (attendance, disciplinary actions, grades, and standardized test scores) will be requested for all students who were in classrooms of participating teachers; these data will be obtained in aggregate at the classroom level and no individual identifiers will be provided to the research team.

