#### Data analytic plan

Basic data screening and descriptives will be conducted for all quantitative variables. We will explore and statistically adjust for baseline equivalence between conditions on all individual outcomes and all school, teacher, and student variables following established guidelines [83]. For all longitudinal modeling, the statistical adjustment will use baseline intercepts as random terms; for dissimilar outcome domains, non-equivalent baseline variables will be included as covariates. Data missing at random will be modeled using full information maximum likelihood estimation or multiple imputation as appropriate.

Unless otherwise indicated, quantitative analyses will employ mixed-effects models using time points nested within classrooms within the school. Standard model-building procedures will be used [84, 85]. Classroom and time trends will be allowed to randomly vary. Piecewise time models will estimate slopes from T1 to T4 (training), T5 through T6 (first month of post-training implementation), T7–T11 (first academic year), and T12–T13 (sustainment during the subsequent year). Variables for condition and condition x time will be added, and iterative models with possible control variables will be tested. Covariates not contributing at *p* < 0.10 based on likelihood ratio tests will be removed. Level 2 and 3 predictors will be fit and excluded for the same reasons. We will obtain estimates of whether there were statistically significant differences among the groups on the rate of change over time (i.e., slope) and whether there are statistically significant group differences in the average score on each outcome variable at the final timepoint of each piecewise segment. Models will be generalized, with appropriate link functions (e.g., log-link, Poisson) applied based on distributional form (e.g., dichotomous, zero-inflation). Estimation will be fit using full maximum likelihood. Models will be assessed for possible violations of assumptions. Goodness-of-fit will be evaluated using likelihood ratios, deviance statistics, and fit criteria. The inference will be evaluated relative to *p* < 0.05. For RQs with multiple DVs, we will adjust for the false discovery rate using Benjamini and Hochberg’s procedure [86].

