We will use thegeneralizer.org to compare our sample to national demographics to examine the generalizability of our findings [58]. If not generalizable, we will use inverse probability weighting to increase the representativeness of estimates [87].*RQ 1a*: A series of 3-level piecewise mixed effects models will be used to test our primary hypotheses: (1) the BASIS-T condition will show steeper gains than the ACC condition from T1 to T2 (e.g., more favorable attitudes towards EBPPs, increased social norms; enhanced task and maintenance self-efficacy; stronger intentions to implement) and (2) both groups will decline after training (T3–T5) as has been found in past TPB research [88], and in the BASIS-T pilot trial [33], but the BASIS-T condition will have longer sustained between-condition effects after training from T3 to T13. Dependent variables will include subscale scores on attitudes, social norms, self-efficacy, intentions, and maintenance self-efficacy.*RQ 1b*: BASIS-T impact on behavioral implementation outcomes will be tested in two ways. First, a mixed effects model will examine whether the proportion of teachers in the BASIS-T condition who adopt PGD (i.e., initiate PGD) is higher than the proportion in the ACC condition. Second, Kaplan–Meier time-to-event analyses will be used to compare conditions on the number of days between training and PGD initiation. Reach will be analyzed using mixed effects models comparing BASIS-T vs. ACC on the proportion of students in each classroom (out of those eligible based on whether their classroom teacher participated in PGD training) who received PGD practices. Impact on PGD fidelity will be analyzed using mixed effects models with sessions within teachers, testing for the main effects of condition on adherence and participant responsiveness ratings derived from both PGD observational and self-report fidelity data. We will test the effects of BASIS-T on PGD sustainment and delayed implementation using the multilevel longitudinal analytic approach described for RQ1a.*RQ1c*: BASIS-T impact on student SEB and academic outcomes will be tested via mixed effects multilevel models as described in RQ1a, with academic data aggregated to the classroom level. Dependent variables will include post-intervention scores on teacher ratings of student behavior.*RQ2a*: Whether mechanisms of behavior change mediate the impact of BASIS-T on implementation outcomes will be analyzed using path analysis [89] extending traditional mediation modeling to a multi-level framework for nested data [90, 91].*RQ2b*: To test whether the effect of BASIS-T on implementation and student outcomes is moderated by teacher factors (e.g., demographics, baseline intentions to implement) and school-level factors, we will add moderators and interaction terms to the analytic approach described in RQs 1a-c.*RQ2c*: To explore what explains “residual” teachers whose implementation behaviors are not accounted for by the mediation model, we will analyze qualitative interviews with teachers who have a difference between predicted (based on BASIS-T putative mechanisms) and actual implementation behavior of ≥ 1 SD. Data will be coded using an integrated directed and conventional content analysis [92] approach as certain codes will be conceptualized during the interview guide development and driven by the exploration, preparation, implementation, sustainment [93] framework (i.e., deductive approach) which will allow for the examination of influences on implementation across multiple levels and phases. Other codes will be developed through a close reading of an initial subset of transcripts (i.e., inductive approach). These themes will provide a way of identifying and understanding the most salient factors that impact implementation and extend beyond the existing BASIS-T mechanisms and theory of change. After a stable set of codes is developed, a consensus process will be used in which all reviewers independently code and compare their coding to arrive at consensus judgments through open dialogue [78, 79, 94].*RQ2d*: We will process cost data by assigning monetary values to each cost. We will use CostOut [95], a web-based program for conducting cost-effectiveness analysis in education, to identify nationally representative unit prices for ingredients. For qualitative data, we will rapidly analyze responses on an ongoing basis [96, 97] and incorporate newly identified costs into future surveys for quantitative measurement.

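### Attendance, discipline and grades are requested only at the end of each school year with no stated pre-training window, so the promised baseline adjustment cannot be done and a whole-year figure for year 1 includes months before training

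*Protocol article*

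**What the plan says.** All references are to the protocol article.

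- **Collection (Quantitative surveys).** "At the end of each school year, academic and behavioral data (attendance, disciplinary actions, grades, and standardized test scores) will be requested". The next clause adds that "these data will be obtained in aggregate at the classroom level and no individual identifiers will be provided to the research team". No term split, date split or prior-year request is named.
- **Timing (same section).** After training come "time 5 two weeks after training, time 6 four weeks after training", then "times 7–11 monthly until the end of the academic year". Times 12 and 13 fall in the following academic year.
- **Baseline adjustment (Data analytic plan).** "We will explore and statistically adjust for baseline equivalence between conditions on all individual outcomes". The same sentence extends this to school, teacher and student variables, and the next one uses baseline intercepts as random terms in longitudinal models.
- **Question (Objectives and aims, RQ 1c).** It asks whether BASIS-T is better at "promoting meaningful changes in student SEB and academic outcomes".
- **Model (Data analytic plan, RQ1c).** Effects are "tested via mixed effects multilevel models as described in RQ1a, with academic data aggregated to the classroom level". The longitudinal models use piecewise slopes over T1 to T4, T5 to T6, T7 to T11 and T12 to T13.

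**The concern.** The analysis section assumes data that the collection section does not supply. For attendance, discipline and grades there is one value per classroom at the end of the training year and one at the end of the sustainment year. Neither precedes training, so nothing is available to adjust for or to start a slope from.

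If the year-1 value covers the whole school year, it also contains a stretch in which no teacher in either arm had been trained. This lowers the sensitivity of the year-1 comparison. These outcomes belong to Aim 1, and the cost-effectiveness analysis computes a ratio for every student outcome measure. A diluted effect would therefore also raise the apparent cost per unit of benefit.

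**Working it through.** **1. The plan's own figure.** The only stated sensitivity figure covering classroom-level variables is the minimum detectable effect size (MDES) of d = 0.37 in the Power section. It rests on 46 schools, 6 teachers per school, a school intraclass correlation (ICC) of 0.10 and 13 timepoints. I assume 80% power, which that section states only for the mediator analyses.

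MDES = M × √(0.10/(0.25×46) + 0.90/(0.25×46×6)) = M × √(0.00870 + 0.01304) = M × 0.1474, where M is the sum of the two t quantiles on 44 degrees of freedom.

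- Two-sided 5%: 0.42.
- One-sided 5%: 0.373.
- Two-sided, 13 timepoints and an assumed teacher-level ICC of 0.52: 0.370.
- Two-sided, with a covariate explaining an assumed 22% of variance at both levels: 0.373.

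So 0.37 is reachable, but only with an input that the article does not give. If it relies on 13 timepoints, it does not carry over to outcomes with one value per year. I use it below only as a yardstick.

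**2. Does any segment of the longitudinal model have enough data?** The year-1 value falls at about T11 and the sustainment-year value at or after T13. None of the four segments holds two values, and T1 to T4 holds none. Slopes and a baseline intercept cannot be estimated for these outcomes.

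**3. Time from training to T11.**

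- Longer case: 4 weeks (0.92 month) + 5 months = 5.92 months.
- Shorter case, with T7 two weeks after T6: 6 weeks (1.38 months) + 4 months = 5.38 months.

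**4. Share of year 1 before training.** f = 1 − (training to year end)/(length of year). The article gives no school-year length, so I assume 9 to 10 months.

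- Year ends at T11: 1 − 5.92/9 = 34% up to 1 − 5.38/10 = 46%.
- Year ends one month after T11: 1 − 6.92/9 = 23% up to 1 − 6.38/10 = 36%.

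The stated 18 months per cohort fits this calendar: 5.9 months + 2 to 3 of summer + 6 to 9 to spring + 0 to 1 of lead-in = 13.9 to 18.9 months.

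**5. Effect on the year-1 comparison.** For a year-averaged rate or grade, the raw arm difference is (1 − f) times the post-training difference. For a cumulative count, the raw difference is unchanged and the extra months add variance. The standardised effect is the same in both cases, because a count is the rate times a constant. Assume equal variance of the two window averages and correlation r between them:

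ratio = (1 − f)/√(f² + (1 − f)² + 2f(1 − f)r)

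| f | ratio, r = 1 | ratio, r = 0.5 | post-training d needed for a whole-year d of 0.37 |
|---|---|---|---|
| 0.23 | 0.77 | 0.85 | 0.48 / 0.44 |
| 1/3 | 0.67 | 0.76 | 0.555 / 0.49 |
| 0.46 | 0.54 | 0.62 | 0.69 / 0.59 |

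The last column is 0.37 divided by each ratio.

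**6. What a baseline covariate could add.** In the step 1 formula (two-sided, one school-level degree of freedom fewer), an assumed R² of 0.22 to 0.50 at both levels lowers the MDES from 0.42 to 0.37 to 0.30. If the covariate explains variance only at school level, the MDES falls to 0.40 to 0.38.

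**The case against.** - **The reference window is unstated, not excluded.** The article fixes when data are requested, not the period they cover. A year-end request could return data by term, and measure details are left to Additional file 4, which is not shown. This stands as a caution: one cannot say that pre-training data will not exist. But the collection schedule is set out in the article, and it offers no baseline for an adjustment that the article promises.
- **The calendar is inferred.** No training month is given. The reason for starting student ratings at time 4 (teachers need enough exposure to the class) hints at earlier training. This stands, so a reader should not take a third of the year as a document figure; the supportable statement is the range.
- **Randomisation already protects the comparison.** Schools are pair-matched on characteristics linked to academic outcomes, and an unadjusted comparison remains valid. This largely stands: the loss is mainly precision and sensitivity. A baseline gains some value because the Randomization section lets trainer availability decide some assignments.
- **These are not the leading outcomes.** The hypotheses labelled primary concern mechanisms, and the RQ1c text names teacher ratings as dependent variables. This limits the weight of the point but does not remove it.

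Three stronger readings are tempting and unsupported. A reader might infer that every year-end value is contaminated, but the sustainment-year data lie wholly after training and test scores are not running totals. A reader might infer bias toward one arm, but the schedule is the same in both. A reader might compare an unadjusted whole-year figure with a baseline-adjusted post-training window and claim a 1.6- to 2.5-fold gain. That figure bundles two changes, assumes correlations of 0.5 to 0.8 and ignores the school level, which is the unit of randomisation.

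**Conclusion.** The point holds in this form. As written, the collection schedule supplies no pre-training value for attendance, discipline, grades or test scores, so the promised baseline adjustment and the RQ1a-type model cannot be applied to them. This conflict does not depend on any calendar assumption.

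Separately, a whole-year figure for year 1 would include roughly 23% to 46% pre-training time, assuming a 9 to 10 month year and at most one month after T11. Under the further assumptions of equal variances and a pre/post correlation of 0.5 to 1, the standardised effect falls to 0.54 to 0.85 of its post-training size. This applies to attendance, discipline and any grade averaged over the year. If grades are final-term only, which the article does not say, it does not apply to them. The precision gain from a baseline covariate cannot be fixed in advance, because the pre/post correlation and the school-level variance are unknown. The change is worth making, but the trial's primary comparisons do not depend on it.

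**What to change.** 1. In the year-end request already planned for the training year, ask for classroom aggregates of attendance and discipline in two windows: school-year start to the school's training date, and training date to year end. For grades, split at the nearest marking period.
2. State the reference window for each outcome. Make the post-training window the year-1 RQ1c outcome and the pre-training window its baseline covariate.
3. For test scores, use a prior-year school- or grade-level aggregate as covariate where available. Make this optional, since tracing the same pupils into earlier classes would be burdensome.
4. Replace the reference to the RQ1a piecewise model for these outcomes with a model that suits one value per classroom per year. Keep the sustainment-year value as a separate comparison.

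The cost is one date split per school in data that remain aggregate and de-identified. Training dates may differ by school, so windows will differ in length and should be expressed as rates, and marking periods will not align exactly. Schools that can supply only whole-year totals should be flagged and handled in a sensitivity analysis. The request should be set before data are drawn, because split figures may be hard to obtain later.

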#### PGD fidelity

Teachers will complete self-reported PGD fidelity assessments, aligned with recommendations to gather reliable and valid data, monthly in the time 4–13 surveys. Additionally, observations to assess the PGD fidelity of the implementing teachers will be conducted by trained school-based personnel using a standard PGD fidelity tool.

#### Qualitative interviews

Teachers whose implementation behavior is insufficiently accounted for by our mediation model (e.g., teachers with favorable implementation outcomes, but who demonstrate low levels of TPB constructs and/or teachers with low implementation outcomes, but high TPB constructs) will be invited to a qualitative interview at the end of the active implementation phase to explore additional implementation determinants. These teachers will be identified at the end of their first year of participation based on the results of statistical modeling, balanced between adopters and non-adopters, and BASIS-T and ACC conditions (15 to 19 interviewees total). Semi-structured phone interviews (approximately 60 min) will be conducted at a convenient time for identified teachers and audio-recorded for transcription and coding purposes.

#### Cost assessments

Cost data collection will occur with all participating teachers to capture major costs of PGD delivery with and without BASIS-T, using activity-based costing to focus on key expenses (e.g., teacher and staff time, materials) [80, 81]. We will measure costs from the payor (i.e., school system) perspective, since the primary costs and associated decision-making would be within the implementing school system in real-world implementation. These data will be collected along with other study measures depending on how often an item needs to be measured (e.g., one-time training prep in time 4 vs. PGD delivery collected monthly alongside the fidelity measures). Following expert guidance to use mixed methods in implementation cost studies [82], we will include open-ended items in each survey asking teachers to identify unexpected resources they have needed for BASIS-T or PGD. ACC costs will be excluded from the cost estimate for the comparison condition; PGD implementation-as-usual is the ideal counterfactual for the cost-effectiveness of BASIS-T because it represents “business as usual” for PGD and, unlike BASIS-T, ACC would never be delivered outside of a research project. To develop complete cost estimates for BASIS-T versus PGD implementation-as-usual, we will combine the teacher-reported data with information from other sources, such as BASIS-T training records and meetings with school partners.

